# The effects of the use of customized silicone digital orthoses on pre-ulcerative lesions and plantar pressure during walking in people with diabetic neuropathy: A study protocol for a randomized controlled trial

**DOI:** 10.1016/j.conctc.2023.101247

**Published:** 2023-12-23

**Keywords:** Diabetes mellitus, Diabetic neuropathies, Diabetic foot, Plantar pressure, Digital orthosis

## Abstract

**Background:**

People with diabetes and diabetic peripheral neuropathy (DPN) often develop calluses due to toe misalignment and increased plantar pressure. Untreated, these issues can progress into ulcers, making early intervention crucial. This trial protocol aims to evaluate the efficacy and safety of customized silicone digital orthoses in preventing ulcers, pre-ulcerative lesions, and peak pressure during gait in people with DPN.

**Methods:**

In this superiority randomized controlled parallel trial with single-blind assessment, 60 participants will be allocated to the control group (CG) or the intervention group (IG). The CG will receive specialized nurse-administered foot care, including callus removal, nail care guidance, and self-care education. The IG will receive the same care plus a customized silicone orthosis for toe realignment for 6 months. Assessments will occur at baseline and 3 and 6 months for the primary outcomes (pre-ulcerative lesions and ulcer incidence) and secondary outcomes (pressure distribution, foot function and health, quality of life, safety, and comfort). Two-way ANOVAs (p < .05) will assess group, time, and group by time effects following an intention-to-treat approach.

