### Trial arms

2.4

Both the IG and CG participants will be instructed to maintain self-care strategies at home, which include proper cleaning, drying the feet and between the toes, moisturizing the skin, and adequate nail trimming. In case of any participant from either group presenting any foot complications, such as a foot ulcer, the participant should immediately notify the researchers and receive guidance from the research team on how to proceed.

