### Outcome assessments and timeline

2.5

Two researchers blinded to group allocation will perform the baseline and all follow-up assessments. IG participants will be assessed at baseline, after 7 days (via a telephone questionnaire about safety and comfort), at 3 months, and at 6 months. CG participants will be assessed at baseline and 3 and 6 months. Intervals of 3 and 6 months were established for the reassessments following the IWGDF guidelines, which recommend that individuals with DM classified as risk 2 need to be evaluated every 3–6 months and with risk 3 every 1–3 months. Table 1 presents the primary and secondary outcomes and the study period in which they will be evaluated according to the SPIRIT guidelines [40].

**Table 1 tbl1:** Primary and secondary outcomes of the study following the SPIRIT guidelines.

Outcomes		When participants will be assessed			
Primary	Measures	Baseline	7 days	3 m	6 m
Pre-ulcerative lesions and ulcers	Assessed according Colagiuri et al. (1995), which classifies hyperkeratosis into 6 grades.	**X**		**X**	**X**
**Secondary**	**Measures**				
Plantar pressure distribution during gait	Pressure peak, pressure-time integral, contact area by anatomical masking	**X**		**X**	**X**
Range of motion (ROM) of metatarsofalgeal joint	To assess ROM, a manual goniometer will be used to assess joint amplitude passively and actively	**X**		**X**	**X**
Toes alignment and flexibility	To measure toes alignment, toes will be photographed with markings on the metatarsophalangeal and interphalangeal joints.	**X**			**X**
Foot health and functionality	FHSQ-BR Domain scores	**X**		**X**	**X**
Quality of life	EQ-5D questionnaire	**X**		**X**	**X**
Satisfaction and safety	Satisfaction and Safety Questionnaires		**X**	**X**	**X**
Comfort	Analog numerical comfort scale		**X**	**X**	**X**

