### Primary and secondary outcomes

2.6

The incidence of ulcers and pre-ulcerative lesions will be considered the primary outcomes. The plantar pressure distribution during walking, metatarsophalangeal joint range of motion (ROM), toe alignment, foot function, overall foot health, quality of life, satisfaction, safety, and comfort will be secondary outcomes.

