#### Pre-ulcerative lesions and ulcers

2.6.1

The assessment of pre-ulcerative lesions (hyperkeratosis) and ulcers will be performed according to the study by Colagiuri et al. [42], in which pre-ulcerative lesions and ulcers were evaluated using six grades, as follows (Fig. 4):1.Grade 1: minimal thickening of the keratin layer2.Grade 2: moderate thickening of the keratin layer3.Grade 3: marked thickening of the keratin layer4.Grade 4: callus with subcutaneous bleeding5.Grade 5: callus with ulcer6.Grade 6: callus with infected ulcer

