**Fig. 4 fig4:**
[figure not shown]
Grades 1 to 6 of severity of pre-ulcerative lesions and ulcers.

Grades 1 to 4 refer to pre-ulcerative lesions, while Grades 5 and 6 are already established ulcers. If the participant is classified as Grade 5 or 6 at baseline assessment, they will not be included in the study but may be included later after the ulcer has healed.

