### Sample calculation and statistical analyses

2.7

The sample size calculation was performed using GPower v. 3.1 software [47] based on the primary outcome variable of the study: the presence of hyperkeratosis (pre-ulcerative lesions). For this outcome, the relative risk (RR) was calculated based on the incidence of hyperkeratosis after treatment with silicone digital orthoses in people with DPN from a previous study [35] using a contingency table. The sample size calculation used the following parameters: RR = 0.4913, test power = 0.80, α = 0.05, and a chi-squared test for contingency tables, resulting in a sample size of 54 participants. Assuming a 10 % loss to follow-up, 60 participants will be needed.

The inferential statistical analysis will be done by adopting an intention-to-treat approach. The imputation of missing values for the analyzed variables will be depend on the nature of the losses. After confirmation of normality (Kolmogorov–Smirnov test), homoscedasticity (Levene test), and imputation of means for missing data of variables with normal distribution, a two-way repeated measures ANOVA will be performed followed by Newman–Keuls post-hoc test to obtain group (CG and IG), time (baseline and 3 and 6 months), and group by time interaction effects. Significant differences will be considered with an alpha of 5 %. For the description of the intervention effect, the effect size (Cohen's d coefficient) and the difference between means with 95 % confidence intervals will be calculated.

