### Data supervision and monitoring

2.9

The data monitoring committee (steering committee) and the Faculdade de Medicina da Universidade de São Paulo Board will regularly monitor (depending on the recruitment numbers and collections performed) the study datasets and make recommendations on necessary protocol modifications or termination of all or part of the study. A trimester meeting will be held to facilitate the study's development. All team members can request meetings as needed. All adverse events occurring during the clinical trial period will be recorded. The patients will be advised to report any discomfort and foot pre-ulcerative signs (e.g., blisters and calluses) or foot ulcers to the main researcher, who will ask for the blinded podiatrist nurse to assist the patient.

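### Ulcer incidence is a primary outcome, but the only measurement stated for it is the foot grade on the 3- and 6-month visit days, and ulcers reported between visits are not linked to it

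*Protocol article*

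**What the plan says.** Section 2.6 of the protocol article states: "The incidence of ulcers and pre-ulcerative lesions will be considered the primary outcomes". The Abstract gives the timing: "Assessments will occur at baseline and 3 and 6 months for the primary outcomes (pre-ulcerative lesions and ulcer incidence").

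The measurement is set in section 2.6.1, following a cited study in which "pre-ulcerative lesions and ulcers were evaluated using six grades"; the text under Fig. 4 adds that "Grades 5 and 6 are already established ulcers". Table 1 marks this outcome at baseline, 3 months and 6 months. Section 2.5 says of the control group that "CG participants will be assessed at baseline and 3 and 6 months". The intervention group has the same visits plus a 7-day telephone questionnaire on safety and comfort. The time factor in section 2.7 is "time (baseline and 3 and 6 months").

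Between visits, section 2.4 says: "In case of any participant from either group presenting any foot complications, such as a foot ulcer, the participant should immediately notify the researchers". Section 2.9 repeats the request, has a blinded podiatrist nurse assist the patient, and states: "All adverse events occurring during the clinical trial period will be recorded". Section 2.4.2 gives adherence as the purpose of the weekly messages.

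**The concern.** Incidence means new ulcers arising over the 6 months. A grade taken on a visit day shows whether an ulcer is open on that day. The two differ for any ulcer that opens after one visit and closes before the next.

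The article itself treats healing as changing a person's status: someone with grade 5 or 6 at baseline may join the trial once the ulcer has healed. By the same logic, an ulcer that opens in week 3 and closes by week 10 would not be grade 5 or 6 at month 3.

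Such an ulcer should already be known to the team, because the participant must report it. What is missing is a link from that report to the primary outcome. At stake are the number of ulcer events in a 60-person trial, the absolute risk in each arm, and whether the result answers the prevention question in the objective.

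**Working it through.** **1. The plan's own figures.** The article gives no figure for ulcers. Its sample size rests on the presence of hyperkeratosis: 54 participants, and 54 / (1 − 0.10) = 60. That number does not depend on how ulcers are counted, so it does not change.

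**2. Routes into the ulcer outcome.**

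| Source of information | Where | Stated purpose | Linked to ulcer outcome? |
|---|---|---|---|
| Six-grade scale at baseline, 3 and 6 months | 2.5, Table 1, 2.6.1 | Primary outcome | Yes |
| Immediate report of a foot ulcer, both arms | 2.4, 2.9 | Guidance and assistance | Not stated |
| Adverse event record | 2.9 | Recording | Not stated |
| Weekly messages | 2.4.2 | Adherence | Not stated |
| 7-day call, intervention group | 2.1, 2.5 | Safety and comfort | Not stated |

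**3. Share of new ulcers missed.** Assumptions: visits at weeks 13 and 26, onset uniform over the 26 weeks, one ulcer per person. Duration is not in the article, so a range is shown. An ulcer of fixed duration d below 13 weeks is open at the next visit only if it began in the last d of the 13 weeks before it. So seen = d/13 and missed = 1 − d/13:

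- d = 4: 1 − 4/13 = 69%
- d = 8: 1 − 8/13 = 38%
- d = 12: 1 − 12/13 = 8%
- d = 13 or more: 0%

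If durations vary exponentially with mean m, seen = (m/13)(1 − exp(−13/m)). This gives 30%, 49%, 61% and 68% at m = 4, 8, 12 and 16, so 70%, 51%, 39% and 32% are missed. When durations vary, a mean above 13 weeks does not remove the loss.

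**4. What this does to the comparison (illustration).** Assume 30 per arm, a true control incidence of 20% and a ratio of 0.4913. The article derives that ratio for hyperkeratosis; applying it to ulcers is an assumption.

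- Expected ulcer cases: 30 × 0.20 × (1 + 0.4913) = 8.9.
- Absolute difference: 0.20 × (1 − 0.4913) = 10.2 percentage points.

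| Fixed duration | Cases seen | Difference seen | Approximate power |
|---|---|---|---|
| Full capture | 8.9 | 10.2 points | 19% |
| 12 weeks | 8.3 | 9.4 points | 18% |
| 8 weeks | 5.5 | 6.3 points | 13% |
| 4 weeks | 2.8 | 3.1 points | 8% |

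Each count and difference is the full-capture value times d/13. With the same d in both arms the factor cancels, so the risk ratio stays at 0.4913.

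**The case against.** The best reply is that the article never says the visit grade is the only source. Table 1 is a schedule of assessments, the time factor belongs to the ANOVA, and an assessor at month 3 could record an ulcer that occurred since baseline. How events between visits are combined may be set out in a fuller document that is not shown. This stands in part: a reader might infer that the plan orders a healed ulcer to be scored as no ulcer, and no sentence says so. The point survives because the article does fix an instrument, a schedule and analysis times for this outcome, and together they do not measure what it is called.

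A reader might also infer that a participant who ulcerated and healed is scored as a prevention success. That goes too far. If the foot shows grade 1 to 4 at the visit, the participant still has a pre-ulcerative lesion, which is also named as primary. Only those with no lesion at all would look lesion-free.

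A third tempting reading is that the comparison is biased in favour of the orthosis. That would need ulcer duration to differ between arms, and nothing in the article suggests it does.

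Finally, fixed-schedule grading by two blinded assessors is a defensible choice. Participants are unmasked, and the intervention arm has at least one extra contact, so counting self-reported events could find more ulcers in that arm. This stands, and it shapes the fix.

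**Conclusion.** The point holds as a mismatch between the named outcome and its stated measurement. Followed as written, the plan gives ulcer prevalence at two visits and would miss ulcers that open and heal between them.

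The documents cannot fix the size of the loss. For a fixed duration it runs from none at 13 weeks or more to 69% at 4 weeks, under uniform onset and one ulcer per person; repeat ulcers would lower the share of participants missed. No single loss figure should be quoted as a finding.

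The consequence is fewer events and a smaller absolute difference, with the risk ratio roughly kept if duration is equal in both arms. Under the illustrative inputs, power for ulcers is only about 19% even with full capture, so the change would not make the ulcer comparison a strong one. It would make the reported incidence mean what it says. This is a cheap improvement and does not threaten the design.

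**What to change.** In section 2.6.1, Table 1 and section 2.7, define the ulcer outcome as at least one new ulcer from randomisation to 6 months. Count an ulcer if it is graded 5 or 6 at a visit, or if it is reported between visits and confirmed by the blinded nurse of section 2.9. Confirmation should not fall to the nurse who makes the orthoses, who section 2.3 says cannot be blinded. Once counted, an ulcer stays counted. At 3 and 6 months, ask both arms the same question about ulcers since the last visit. Keep the visit-day grade as a separate severity outcome.

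Show a sensitivity analysis limited to ulcers graded by the blinded assessors at visits, because between-visit events depend on unmasked participants reporting them and contact is unequal between arms.

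The cost is small: a change of wording, one added question at existing visits, and a confirmation record for each reported ulcer. No extra visits or participants are needed. Recruitment is under way (section 3.1), so the change should be made before outcomes are analysed by arm and reported to the funders and the registry, as section 2.1 requires for important modifications.

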**Conclusion:**

Although recommended for foot ulcer prevention, custom silicone orthosis adoption remains limited due to the low certainty of evidence. This trial seeks to provide more consistent evidence for the use of toe orthoses in preventing callus and ulcer formation for individuals with DPN.

**Trial registry:**

ClinicalTrials.gov (NCT 05683106) “Effects of Customized Silicone Digital Orthoses in People with Diabetic Neuropathy” (registered on December 20, 2022).

## Introduction

1

The prevalence of diabetes mellitus (DM) continues to rise worldwide. According to the latest data, 537 million people between 20 and 79 years of age are affected by DM, corresponding to 9.8 % of the global population [1]. The new estimate is that 643 million people will be affected by DM by 2030 [1]. Poorly controlled DM, associated with DM progression, leads to multiple long-term complications, including diabetic peripheral neuropathy (DPN), diabetic foot ulcers, amputation, and premature death [[2], [3], [4]] [[2], [3], [4]] [[2], [3], [4]].

DPN affects approximately 50 % of people with DM and is considered a first-degree risk factor for developing foot ulcers [5]. DPN is caused by damage to the somatic fibers, which leads to reduced or absent foot sensitivity, decreased proprioception, muscle loss, and postural instability [6]. Another major finding in people with DPN is motor impairments, such as decreased foot-ankle range of motion [7,8]; atrophy of the intrinsic and extrinsic foot-ankle muscles [[9], [10], [11]]; alteration of the biomechanical properties of connective tissue, such as increased hardness of plantar tissue [12] and increased soft tissue thickness and stiffness [13]; alterations in the lower limbs’ muscle activation [14]; decreased conduction velocity of the tibialis anterior [15]; changes in torque generation strategy from the ankle to the hip [16]; alteration of the plantar arches [17]; decrease or displacement of fat pads from the hallux and toes [18]; forefoot and toe deformities, such as claw, hammer, and mallet toe and hallux valgus [19]; prominences of the metatarsal heads [20]; and changes in foot rollover and gait biomechanics [21].

All of these biomechanical and musculoskeletal alterations cause changes in the plantar pressure distribution during gait [22,23], increasing peak pressures, especially at the forefoot. When associated with the loss of protective sensation, those peak pressure increases could culminate in the formation of hyperkeratosis, which is the most classic manifestation on the feet of people with DPN [24]. Hyperkeratosis confers a 11-fold risk for developing an ulcer [25] and is the second most common cause of ulcer recurrence [26]; thus, prevention and timely treatment are crucial to reduce ulcer incidence and recurrence [27]. Approximately 97 % of foot ulcers develop at the forefoot region, with 58 % of these ulcers developing at the hallux and other toes and 39 % at the metatarsal heads [28]. Thus, as most ulcers occur at the forefoot region [[29], [30], [31]] [[29], [30], [31]] [[29], [30], [31]], strategies for ulcer prevention should consider this region the most critical.

The recommended treatment for hyperkeratosis includes debridement and redistribution of plantar pressure on the metatarsal heads and toes [32]. One of the most common procedures is callus debridement, which can result in a reduction of around 26 % of peak pressure over the treated areas [33]. Although debridement is important to reduce hyperkeratosis, it is a palliative approach; if the cause of hyperkeratosis formation (mechanical stresses) is not dealt with quickly, hyperkeratosis will form again. Therefore, it is necessary to adopt strategies to redistribute plantar pressure over the toes and metatarsal heads to reduce abundant calluses and ulcer formation.

One of the strategies that can be adopted for plantar pressure redistribution is toe realignment through customized silicone digital orthoses, recently recommended by the guidelines of the International Working Group on the Diabetic Foot (IWGDF) [32]. However, studies demonstrating the efficacy of silicone digital orthoses for preventing hyperkeratosis are still very limited and of low scientific quality [32,34]. Only one randomized controlled trial has demonstrated that the use of custom orthoses on the forefoot of people with DPN and a high risk of ulceration is safe and reduced the incidence of new pre-ulcer lesions over a 3-month period [35]. In addition, a prospective study indicated that customized silicone digital orthoses were effective for reducing 10 % of peak pressure during gait in people with toe deformities after 18 months, with 82 % of the participants reporting improvements in their gait pattern [36]. There is also some evidence of the effectiveness of this approach in the short term in people with calluses from different etiologies. Leather, gel, and silicone orthoses were shown to acutely reduce 40–50 % of the plantar load at the second toe apex during gait in people with calluses associated with claw or hammer toes [37]. Additionally, customized silicone orthoses alone acutely reduced 30 % of the peak pressure under the toes, but the association of a debridement procedure with customized silicone orthoses reduced the plantar pressure by 54 % in individuals with DPN and calluses in the distal phalanges of the toes [38].

Given this context, silicone digital orthoses, which are non-invasive, customizable using molds made by professionals with prior training, inexpensive, and easy to handle for the users, may be a promising alternative to reduce the risk of ulcerations on the feet of individuals with DPN associated with motor deformities by reducing hyperkeratosis [39]. Thus, the objective of this trial is to evaluate the efficacy and safety of using customized silicone digital orthoses for 6 months compared to the usual recommended podiatric care [32] for the prevention of ulcers and pre-ulcerative lesions at the forefoot and the reduction of peak pressures during gait in people with DPN [32].

## Methods

2

### Trial design and setting

2.1

This will be a superiority controlled clinical parallel trial with random allocation and single-blind assessment. The trial has been approved by the Research Ethics Committee of the School of Medicine at USP (CAAE 65204622.4.0000.0068, 11/24/2022) and registered with ClinicalTrials.gov (NCT05683106, 12/20/2022). Any important protocol modifications will be reported to the relevant parties (funding sources and trial registration). This trial will have an allocation ratio of 1:1 and will follow all SPIRIT recommendations [40]. Fig. 1 presents a flowchart with the steps for the clinical trial.

**Fig. 1 fig1:**
[figure not shown]
**-** Flowchart showing the stages of the clinical trial.

The trial will be conducted with individuals who have DPN and forefoot deformities (IWGDF risk categories 2 and 3). The participants will be allocated randomly to either the control group(CG), which will receive guidance on preventive foot care and callus debridement, or to the intervention group(IG), which will receive guidance on preventive foot care, callus debridement, and customized silicone digital orthoses according to the forefoot deformity. The CG and IG will receive guidance regarding the use of therapeutic insoles and footwear according to individual needs. IG participants will be evaluated at baseline, 1 week after baseline to inquire about the safety and comfort of the orthoses, and at 3 and 6 months for follow-up measurements. CG participants will be evaluated at baseline and 3 and 6 months after allocation. The assessments will be carried out at a nursing clinic specialized in stomatherapy, where the main researcher performs clinical activities focusing on individuals with DPN.

### Participants and recruitment

2.2

Participants will be recruited from private clinics linked to the Brazilian Unified Health System (Sistema Unico de Saúde; SUS) that are specialized in preventing and treating the diabetic foot as well as from clinics specialized in treating wounds. Participants will undergo an initial assessment for screening and confirmation of eligibility criteria. Inclusion criteria will be people of both sexes ages 18–75 years who are diagnosed with type 1 or 2 DM with DPN as confirmed by loss of sensitivity measured by Semmes–Weinstein 10-g monofilament, a 128-Hz tuning fork, and the fuzzy score of DPN severity (www.usp.br/labimph/fuzzy); have one or more forefoot flexible deformities (claw, hammer, mallet, or overlapping toes; bunion; prominences of the metatarsal heads; or decrease/displacement of adipose cushion); and are able to independently walk with or without an assistive device. The non-inclusion criteria will be other diagnosed neurological diseases, major vascular complications, receiving any physiotherapy interventions for the lower limbs during the entire intervention period, not performing foot-ankle exercises, having a callus grade 5 or 6 at baseline, major amputations in both limbs (above the ankle), minor amputations in the foot that will receive the orthosis (Chopart, Lisfranc, transmetatarsal), and the presence of dementia or inability to provide consistent information.

